**Protocol Abstract**

| **Project name** | Efficacy of tranexamic acid in patients undergoing huge meningioma resection |
| --- | --- |
| **Objectives of research** | 1. To investigate the effect of tranexamic acid (TXA) on blood loss during the resection of huge meningioma. 2. To investigate the effects of TXA on coagulation function, blood salvage, transfusion of allogeneic blood products in patients undergoing huge meningioma resection; to investigate the effect of TXA on the resection of huge meningioma and the hemostasis of surgical field after resection.   3、To investigate the effect of TXA on epilepsy and other adverse events after resection of huge meningioma.  4、To investigate the effects of TXA on length of stay, ICU stay and hospital charge of patients after resection of huge meningioma. |
| **Study design** | Prospective, single-center, randomized, controlled, double-blinded trial |
| **Sample size** | 228 cases |
| **Study population** | Inclusion criteria ***Preoperative computed tomography (CT), or magnetic resonance imaging (MRI) suggested supratentorial meningioma with diameter no less than 5cm in any of three axes.*** 2）Patients aged between 18 and 65 years.  3）American Society of Anesthesiologist (ASA) physical status Ⅰ to Ⅲ.  4）Written informed consent obtained. |
| Exclusion criteria   1. Allergic to TXA. 2. With a history of thrombotic disease. 3. Under anticoagulant or antiplatelet therapy. |
| **Treatment protocol** | After confirming that the patients meeting the inclusion criteria, patients were randomly assigned to one of 3 groups: high-dose group, low-dose group and control group. The high-dose group was given a loading dose of 20mg/kg TXA within 10 minutes after induction, followed by a continuous infusion of TXA at a rate of 5mg/kg/hour. Low-dose group received a loading dose of 20mg/kg TXA within 10 minutes, and then continued infusion of identical volume of normal saline. Control group was given identical volume of normal saline. Follow-up will be conducted during the operation, 1-5 days after operation, and 6 months after operation to collect data. |
| **Outcome and safety measures** | Primary outcome: the estimated cumulative intraoperative blood loss  Secondary outcome:   1. Intraoperative coagulation function. 2. Calculated blood loss. 3. Intraoperative cell salvage use and allogeneic blood products use. 4. Simpson grading scale for the extent of meningioma resection. |

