**1. Study design**

1）Study design: The study is a prospective, randomized, controlled, double-blinded trial.

2）Randomization: Using computer software to generate random sequences, patients were randomly assigned to one of three groups (high-dose, low-dose or control group）based on the grouping of random numbers with a 1:1:1 ratio.

3）Blinding: The participants, responsible anesthesiologists, neurosurgeons, and outcome assessors will all be blinded to the allocation until the completion of the study analysis.

4）Research center: Department of Anesthesiology, Beijing Tiantan Hospital, Capital Medical University.

5）Sample size: 228 cases.

6）Rationality and basis of indications: Currently, clinical studies on TXA are mainly limited to orthopedics, obstetrics, cardiac surgery, trauma, etc., and there are few studies in neurosurgery. However, huge meningioma is prone to massive intraoperative bleeding due to its huge tumor volume, rich blood supply, vascular invasion, and cranial nerve damage caused by the tumor. Previous randomized controlled trials of the effect of TXA on intraoperative blood loss in meningioma found that TXA significantly reduced intraoperative blood loss. However, the study sample size was small, and the tumor locations were highly heterogeneous, so the results of these studies cannot be applied to the population of huge meningioma. The purpose of this study is to investigate the effect of TXA on intraoperative blood loss in meningiomas with a diameter over 5cm. At present, our institution has confirmed the safety of TXA in regard to postoperative seizure in patients undergoing meningioma resection, and the efficacy of TXA needs to be further investigated.

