3. **Grouping and intervention:** Participants were randomly divided into three groups: low-dose group, high-dose group, and placebo (control group). Intravenous infusion of TXA or placebo (saline) will be initiated after anesthesia induction. The research drug is TXA manufacturer in 2mL with 200mg. Patients in the high-dose group will receive an intravenous infusion of 20mg/kg TXA followed by a continuous infusion of 5mg/kg/h until the end of the operation. Patients in the low-dose group will receive 20mg/kg intravenously TXA only. Patients in the control group will receive an identical volume of 0.9% normal saline. Both TXA and saline for a single infusion were stored in a 100ml container sheltered from light, and the infusion rate was 250ml/h.
4. Standard anesthesia management: After establishing reliable venous access, standard monitoring, including routine electrocardiograph (ECG), non-invasive blood pressure, pulse oxygen saturation, end-tidal carbon dioxide, and bispectral index (BIS) monitoring will be initiated. After pre-oxygenation for 6min, standardized anesthesia induction will be initiated with propofol 1-2mg/kg or etomidate 0.2mg/kg, sufentanil 0.2-0.4ug/kg, rocuronium 0.9mg/kg or cisatracurium 0.2mg/kg. The actual dose can be adjusted according to the patient's physiological condition. Intraoperative anesthesia can be maintained by intravenous anesthesia or combined with intravenous anesthesia, and the intraoperative BIS will be maintained between 40 and 60. H3 receptor blocker (Tropisetron 5mg) will be administered before the end of surgery to prevent nausea and vomiting. All medications will be recorded in detail, and patients will be transferred to the ward or post-anesthesia care unit (PACU) or ICU. Patient-controlled analgesia devices were routinely used after surgery, and sufentanil was selected as the analgesic formulation. The dosage was determined by the anesthesiologist in charge. If the subject still presented severe postoperative pain (visual analogue scale (VAS) ≥5, with agitation), other rescue analgesic drugs will be administered by the physician in charge and be recorded in detail.
5. **Concomitant medication**

This study focuses on clinical anesthesia, anesthesia drugs can be concomitant drugs.

1. **Trial procedures**

**Enrollment:** 1）Whether it meets the inclusion criteria; 2) Whether it meets the exclusion criterion; 3) Informed consent; 4) Randomization.

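### The two descriptions of the low-dose arm disagree on a saline maintenance infusion; followed literally, the intervention section lets operating-room staff identify at least one arm

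*Protocol*

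**What the plan says.** The treatment row of the Protocol Abstract describes two phases for the low-dose arm: "Low-dose group received a loading dose of 20mg/kg TXA within 10 minutes, and then continued infusion of identical volume of normal saline". For the control arm it says: "Control group was given identical volume of normal saline".

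The grouping and intervention item under Study method describes the arms differently. The high-dose arm has its loading dose, "followed by a continuous infusion of 5mg/kg/h until the end of the operation". For the low-dose arm: "Patients in the low-dose group will receive 20mg/kg intravenously TXA only". For the control arm: "Patients in the control group will receive an identical volume of 0.9% normal saline". The only matched presentation described there concerns the single infusion: "Both TXA and saline for a single infusion were stored in a 100ml container sheltered from light".

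On masking, the Study design section states: "The participants, responsible anesthesiologists, neurosurgeons, and outcome assessors will all be blinded to the allocation until the completion of the study analysis". The blinding item under Study method repeats this for participants, anesthesiologists and post-operative assessors. It adds that an investigator outside the intervention and follow-up prepares TXA and placebo and labels the container as research drug.

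**The concern.** A bolus-plus-infusion arm can be masked against a bolus-only arm only if the bolus-only arm also has a dummy infusion. The abstract provides one for the low-dose arm. The section that sets out the intervention in detail does not mention it, and its wording can be taken to exclude it. If staff work from that section, a pump that is running in some patients and absent in others shows the anesthesiologist and surgeon something about the allocation.

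This matters because the data are generated in the same room during the infusion. Under Outcome assessments, the primary outcome is suction volume minus flushing plus gauze. The hemostasis scores are ratings of the operative field, and one trigger for plasma, cryoprecipitate and platelets is a judgement that bleeding is diffuse. Use of topical hemostatic agents is also recorded intraoperatively. The high-versus-low comparison is the most exposed, because it isolates the maintenance infusion and the maintenance infusion is what would be visible.

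**Working it through.** **Step 1: set the two sections side by side.**

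| Arm | Abstract: after the loading phase | Study method: after the loading phase |
| --- | --- | --- |
| High-dose | TXA infusion | TXA infusion |
| Low-dose | saline infusion, identical volume | none mentioned; TXA loading dose 'only' |
| Control | saline, identical volume | saline, identical volume; arm matched not stated |

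In the abstract the two active arms have the same volumes, so identical volume has one meaning for control, and every patient has a loading and a maintenance infusion. The blind is kept. Under Study method, read literally, the two active arms have different volumes, so identical volume has two possible meanings.

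**Step 2: follow each literal reading of the Study method item.**

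| Reading | Arms with a running infusion | Arm identified | Comparisons exposed | Comparison still masked |
| --- | --- | --- | --- | --- |
| (a) control matched to low-dose | high-dose | high-dose | high vs low, high vs control | low vs control |
| (b) control matched to high-dose | high-dose, control | low-dose | high vs low, low vs control | high vs control |

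On either reading one arm of 76 is identified and two of three comparisons are exposed. High versus low is exposed on both.

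**Step 3: look for text that settles it.** The blinding item under Study method covers preparation and labelling of the container but does not mention a second, dummy infusion. The table of modifications at the end has an entry on when the TXA infusion ends, but none on a saline maintenance infusion. Nothing in the protocol resolves the difference.

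**Step 4: illustrate what a bias would do.** The protocol gives no figure for this, so the bias sizes are assumed.

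- Inputs from the protocol: SD 400 mL, 76 per group, dropout 2.5%, pairwise alpha 0.017.
- Assumptions: a two-sided test (the protocol does not say), and bias of 0, 50 or 100 mL in the difference between two arms with no true difference. 50 mL and 100 mL are 5% and 10% of the assumed 1000 mL.
- Evaluable per arm: 76 × 0.975 = 74.1, taken as 74.
- Standard error: 400 × √(2/74) = 65.8 mL.
- Critical t, 146 degrees of freedom, two-sided 0.017: 2.414.
- Noncentrality = bias / 65.8. Rejection probability = P(|T| > 2.414) under the noncentral t distribution.

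As a check on the set-up, the protocol's own effect of 250 mL gives noncentrality 3.80 and power 91.6%, in line with the stated 90%.

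| Assumed bias | Noncentrality | Probability of a significant result |
| --- | --- | --- |
| 0 mL | 0 | 1.7% |
| 50 mL | 0.76 | 5.2% |
| 100 mL | 1.52 | 18.9% |

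**The case against.** A reader might infer that a running pump gives away the high-dose arm and that the double blind therefore fails. The protocol does not support either step as a plain statement. The high-dose arm is singled out only if control has no maintenance infusion, and the Study method item leaves that open. If control is matched to high-dose, it is the low-dose arm that stands out.

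Failure of the blind is also conditional. The word 'only' can be read as limiting the TXA, with the abstract supplying what else is infused, so that both descriptions are true. The stated blinding of anesthesiologists and neurosurgeons favours that reading, as does preparation by an investigator outside the intervention. The trial runs at one center, so no remote site is working from the intervention item alone. This all stands, and it limits the point to a literal reading of one section. It does not remove the point: staff would have to let the abstract override the detailed section, and a masking procedure should not depend on that inference.

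The outcomes are also not wholly subjective. The primary outcome is a volume formula, red-cell transfusion has hemoglobin and hematocrit triggers, plasma products have laboratory triggers, and a hematocrit-based blood loss is collected as well. This also stands, so it cannot be said that knowing the arm would shift every outcome. The hemostasis scores and the diffuse-bleeding trigger remain matters of judgement.

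Finally, nothing in the protocol supports 50 or 100 mL as the likely bias. That is correct; those figures show sensitivity only.

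**Conclusion.** The point holds in a conditional form. The abstract and the Study method item differ on whether the low-dose arm has a saline maintenance infusion, and the latter leaves the control volume undefined. Followed literally, the Study method item makes at least one arm of 76 identifiable during surgery and exposes two of the three pairwise comparisons, always including high versus low. That contradicts the blinding required in the Study design section. Which arm is identified depends on how control is matched.

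This is more than a missing detail, because it bears on the blind while the primary outcome is being collected. The size and direction of any bias are unknown. The rise from 1.7% to about 5% (50 mL) or 19% (100 mL) rests on the assumed bias sizes, a two-sided test, 74 evaluable patients per arm and the protocol's SD of 400 mL. The inconsistency itself does not depend on those assumptions.

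**What to change.** Reconcile the Protocol Abstract and the grouping and intervention item so that both state the same things:

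- for each of the three arms, what is infused in the loading phase and what in the maintenance phase;
- what identical volume refers to for the control arm;
- that the placebo maintenance infusion the abstract already plans for the low-dose arm is part of the procedure, and that infusions are presented so that the arms cannot be told apart, as the Study design section requires.

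The wording that gives the low-dose arm TXA 'only' should be clarified so that it cannot be read as excluding a saline infusion. The active doses are not in question and stay as they are; infusion rates and stopping points are for the investigators to state consistently. The cost is a wording change, plus labelled saline for patients who would otherwise have no maintenance infusion. No change to the sample size is needed.

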**2. Sample size and study project**

According to previous studies, the intraoperative blood loss for huge meningioma was about 1000ml, and the overall standard deviation of the population was about 400ml. A single TXA infusion was assumed to be effective in reducing blood loss by about 25%, and continuous TXA infusion could further reduce blood loss by 25%, so the minimum effect size was 250ml. A sample size of 228 patients (76 per group) is calculated to provide 90% power to detect the between-group difference at a significance level 𝛼 of 0.017 and the overall type I error of 0.05, with a dropout rate of 2.5% with Bonferroni adjustment.

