**Peri-operation:** Baseline characteristics, family history, medical history, physical examination, preoperative lab test (blood routine, coagulation function and chemistry panel), preliminary radiology diagnosis, pre-operative evaluation (GCS score, Charlson complications score, ASA classificaiton, Karnofsky score, Caprini thrombosis risk score).

**Intraoperative:** 1) target mean arterial pressure; 2) cranial nerve block; 3) use of positive inotropic drugs or vasopressor; 4) average inhaled oxygen concentration; 5) coagulation; 6) arterial blood gas (ABG) test; 7) estimated blood loss; 8) type and volume of allogenic transfusion; 9) intraoperative adverse events; 10) tumor resection extension; 11) surgical hemostasis score and hemostasis difficulty; 12) use of topical hemostatic agents; 13) anesthetic drugs; 14) anesthetic parameters; 15) physiological parameters.

**PACU：**1) time of PACU admission; 2) PACU events; 3) drug use; 4) time of PACU discharge.

**Day 1**: 1) outcomes: assessment time, KPS score, GCS score, postoperative epilepsy, embolism, infection, postoperative hematoma, re-operation, ICU admission, death, other adverse events, and assessment of neurological dysfunction; 2) laboratory test; 3) assessment of thrombosis risk by Caprini score.

**Day 3**: outcomes: assessment time, postoperative epilepsy, embolism, infection, postoperative hematoma, re-operation, ICU admission, death, other adverse events, and assessment of neurological dysfunction.

**Day 5±2**: 1) outcomes: assessment time, death, postoperative epilepsy, embolism, infection, postoperative hematoma, re-operation, ICU admission, other adverse events, and assessment of neurological dysfunction; 2) Brice Awareness Questionnaire 5±2 days after surgery; 3) postoperative brain image and EEG.

**Discharge:** 1) pathology diagnosis; 2) discharge summary (date of discharge, recovery, length of stay, referral, length of stay in ICU, hospital charges, epilepsy medication); 3) postoperative treatment plan; 4) clinical assessment (anemia, epilepsy, embolism, infection, hematoma, re-operation, blood transfusion, etc.).

**180 days**: 1) outcomes: assessment time, death, KPS score, GCS score, postoperative epilepsy, embolism, infection, postoperative hematoma, re-operation, ICU admission, other adverse events, and assessment of neurological dysfunction.

1. **Follow-up period**

**Follow-up period:** the day before surgery, 1, 3, 5±2 and 180 days after surgery.

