**Follow-up items:** examination (blood routine, coagulation function and chemistry panel) on the first day after surgery, Caprini risk score on the first day after surgery, KPS score on postoperative day 1, day 3, day 5 ±2 and at discharge and on 180 days. Others include GCS score and complication evaluation.

1. **Outcome assessments**

The primary outcome is the estimated cumulative intraoperative blood loss, which is calculated using the formula: collected blood volume in the suction canister (mL) – the volume of flushing (mL) + the volume from the gauze tampon (mL).

The secondary outcomes include:

1. Intraoperative coagulation function monitoring assessed by rapid TEG at the beginning and the end of the operation.
2. Calculated blood loss: Calculated blood loss = estimated blood volume×(Hcti−Hctf)+transfused RBC volume]/Hctmean.
3. Intraoperative cell salvage use and allogeneic blood products use. The indications for routine blood transfusion in our institution are as follow:

**a.** Hb < 9g/dl or Hct < 30%. If the intraoperative pathology consultation indicated a WHO classification of II or I, we will first consider cell salvage. If intraoperative pathology was unavailable or WHO classification > II, allogeneic blood transfusion will be preferred.

**b.** Use of frozen plasma, cryoprecipitate, and platelet products, will be initiated based on the American Society of Anesthesiologists Task Force on Blood Component Therapy: PT/APTT is more than 1.5 times prolonged, fibrinogen <1g/L, or diffuse microvascular bleeding at the surgical field (although there is no surgical hemostasis and/or no visible clots in the surgical field).

1. Simpson grading system for the extent of meningioma resection.
2. Hemostasis: Hooda score.
3. Operative field surgical hemostasis score using VAS score.

Safety outcome includes 1) frequency and episodes of postoperative seizure; 2) other intraoperative complications (allergy, hypoxemia, refractory hypotension, pulmonary embolism, etc.) other postoperative complications (venous thrombosis, new cerebral ischemia, intracranial hematoma, hydrocephalus, infection, abnormal renal function, myocardial infarction).

Economic outcome: 1) ICU admission, length of ICU stays; 2) length of hospital stay and hospital charge.

1. **Potential risks, benefits of the project & risk management**

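### The primary blood-loss formula has no term for blood collected by cell salvage, so as written it can understate loss in salvaged patients and pull the estimated effect toward zero

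*Protocol*

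**What the plan says.** In Outcome assessments, the primary outcome is an explicit sum: "collected blood volume in the suction canister (mL) – the volume of flushing (mL) + the volume from the gauze tampon (mL"). It has three components and none refers to cell salvage.

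Secondary outcome 3 in the same section, also listed in the Protocol Abstract, is "Intraoperative cell salvage use and allogeneic blood products use". Under it stand the institution's transfusion indications. The trigger is "Hb < 9g/dl or Hct < 30" per cent, and then: "If the intraoperative pathology consultation indicated a WHO classification of II or I, we will first consider cell salvage". With a higher grade, or with no intraoperative pathology, allogeneic blood is preferred.

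The Intraoperative list under Trial procedures includes estimated blood loss and "type and volume of allogenic transfusion". It has no item for the volume collected by salvage.

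The protocol does not say when salvage collection starts, whether the salvage reservoir is a different vessel from the suction canister, or whether its contents are counted.

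**The concern.** The formula is the trial's primary measurement, and the protocol itself expects a procedure that can take shed blood out of the vessel being measured. That procedure follows a fall in haemoglobin or haematocrit. Blood loss drives that fall, and the trial's hypothesis is that tranexamic acid reduces blood loss. Any uncounted volume would therefore be related to treatment: more would be missed in the arm that bleeds more, and the mean difference would shrink.

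The pathology condition adds a second distortion. Two patients with the same true loss could receive different values because one has a grade I or II tumour on intraoperative pathology, while the other has a higher grade or no result. Randomisation balances this between arms on average, but the millilitres saved would still depend on the case mix and on whether pathology is available.

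What is at stake is the trial's main result, the millilitres saved, even where significance survives. Without a recorded reservoir volume, the error could not be corrected afterwards.

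**Working it through.** **Planning inputs (Sample size and study project; Statistics).** Control mean: "the intraoperative blood loss for huge meningioma was about 1000ml". Spread: "the overall standard deviation of the population was about 400ml". Difference 250 mL, alpha 0.017 per comparison (taken as two-sided), power 90%, dropout 2.5%, 76 per group, 228 in total.

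**Reproducing 228.** A two-sample t-test with effect 250/400 = 0.625 needs 70.3 per group, so 71. Then 71/0.975 = 72.8, so 73 per group and 219 in total. Dividing by the Mann-Whitney efficiency for normal data, 0.955 (an inference; the protocol does not state it), gives 70.3/0.955 = 73.7, so 74. Then 74/0.975 = 75.9, so 76 per group and 228 in total. Evaluable patients: 76 × 0.975 = 74 per group. With 74 per group, SD 400 and alpha 0.05/3, t-test power for 250 mL is 0.915.

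**Effect on the mean difference.** The documents give no salvage rates or volumes, so these are assumptions. Let a share p_C of controls and p_T of treated patients be salvaged, with V mL uncounted in each.

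Measured difference = 250 − (p_C − p_T) × V

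- 20% vs 10%, V = 500: 250 − 0.10 × 500 = 200 mL.
- 30% vs 15%, V = 600: 250 − 0.15 × 600 = 160 mL.

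**Effect on power.** The SD does not stay at 400. With normal losses and salvage triggered by a variable that has correlation ρ with blood loss, the variance of measured loss in an arm is

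400² + V²p(1 − p) − 2Vρ × 400 × φ(z_p),

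where φ(z_p) is the standard normal density at the cut-off leaving a share p above it: 0.2800, 0.1755, 0.3477 and 0.2332 for p = 0.20, 0.10, 0.30 and 0.15.

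Worked case, 30% vs 15%, V = 600, ρ = 0.6:
- Control: 160,000 + 75,600 − 100,135 = 135,465.
- Treated: 160,000 + 45,900 − 67,150 = 138,750.
- Average variance 137,108, so SD 370. Effect 160/370 = 0.432, power 0.58.

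| Salvage rates, V | Measured difference | ρ | SD | Power (74 per group, alpha 0.05/3) |
|---|---|---|---|---|
| None omitted | 250 mL | – | 400 | 0.915 |
| 20% vs 10%, 500 mL | 200 mL | 1.0 | 316 | 0.92 |
| 20% vs 10%, 500 mL | 200 mL | 0.6 | 370 | 0.81 |
| 30% vs 15%, 600 mL | 160 mL | 1.0 | 285 | 0.84 |
| 30% vs 15%, 600 mL | 160 mL | 0.6 | 370 | 0.58 |

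At ρ = 0.58 the last row gives 0.57. With lognormal losses and ρ = 1, simulation gives 0.96 and 0.90 for the two scenarios. The 57% figure is not a floor: at ρ = 0.5 the second scenario gives 0.53.

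**A different mechanism.** Suppose instead that 25% to 100% of the loss above 800, 1000 or 1500 mL goes uncounted. In simulation, true differences of 245 mL (normal losses truncated at zero) and 250 mL (lognormal) were measured as 246 down to 103 mL. Power at alpha 0.017 was 0.76-0.92 for normal and 0.94-0.99 for lognormal losses. The mean difference shrank in every case. Power did not always fall.

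**If the reservoir is already counted as canister volume,** V = 0 and there is no bias.

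**The case against.** The strongest reply is that diversion is not documented. The haemoglobin and haematocrit threshold stands under transfusion indications, and the text says only "we will first consider cell salvage". The outcome is described as cumulative loss, and a team might well count the reservoir as suction volume. This stands, and it makes the bias conditional. It does not supply the missing term: read literally, the formula leaves the reservoir out, and no salvage-collected volume is listed to add back.

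A reader might infer that the heaviest bleeders are the ones undercounted. That holds only on average. Those with a higher-grade tumour or no intraoperative pathology are directed to allogeneic blood, so their shed blood stays in the formula. The trigger also depends on baseline haemoglobin and dilution.

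A reader might also infer that the stated 90% power is lost, since holding the SD at 400 gives 73% for 200 mL and 51% for 160 mL. The documents do not support that. Removing volume from patients who bleed more changes the SD, and power may be fully retained.

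Two further replies have some force. Bias toward no effect does not create a false benefit, but it does misstate the size of the benefit. Calculated blood loss from haematocrit does not depend on canister contents and offers a cross-check. However, its transfused red-cell term does not say whether re-infused salvaged cells count. If they do not, loss is understated in the same patients.

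**Conclusion.** The concern holds as a fault in the stated definition: the primary outcome formula does not account for blood collected by a procedure that the protocol itself foresees, and no such volume is listed for recording. If the reservoir is separate from the canister, and salvage is more frequent in the arm that bleeds more, the estimated difference is biased toward zero.

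The size cannot be derived from the documents. Under the assumed rates and volumes, a true 250 mL is measured as roughly 160-200 mL, an understatement of 50-90 mL or 20-36%. Lost power is possible but conditional: near 90% if salvage follows blood loss closely, about 57% under a moderate link in the less favourable scenario. The shrunken estimate is the dependable consequence; a particular loss of power is not.

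**What to change.** Define the primary outcome as: suction canister volume + salvage reservoir volume before washing − all irrigation − anticoagulant or other fluid entering the reservoir + gauze volume. If the reservoir is already treated as canister volume, say so in one sentence and subtract the same fluids.

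Record reservoir volume and anticoagulant volume on the case report form. State whether re-infused salvaged red cells count in the transfused red-cell volume used for calculated blood loss.

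The cost is a change of wording and two extra fields, assuming the salvage device gives these readings, which the protocol does not describe. Patient care does not change. Nor does the sample size, since the planning mean and SD are not tied to either definition.
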